### Recruitment process

Multiple recruitment strategies will be used for MAGDA-DPP. The study will be promoted by mailed leaflets via the National Diabetes Services Scheme (NDSS) (using data from the National GDM Register) [20] to women living in relevant postcodes in Adelaide (South Australia) and Melbourne (Victoria). Women will be recruited predominantly through participating hospitals, referrals from private healthcare providers and retrospective database mining of hospital records. Other specific recruitment activities may be used in consultation with the diabetes education service at each hospital. Women diagnosed with GDM will be informed about the study by diabetes educators, either individually or in a group.

Prospective recruitment will take place at The Royal Women’s Hospital and Sunshine Hospital in Melbourne and Lyell McEwin Hospital in Adelaide. Because of late participation in the study by Women’s and Children’s Hospital and Flinders Medical Centre in Adelaide, retrospective as well as prospective recruitment will take place at these hospitals only, allowing women diagnosed with GDM after July 1, 2011 to participate in the study (Table 1).

At the hospital recruitment sites, women newly diagnosed with GDM will be referred, if they agree, to the MAGDA recruiter. Alternatively, potential participants will be identified by their medical history or from the list of newly diagnosed patients, with the assistance of the clinic coordinator. Women will be approached by the recruiter in the antenatal clinic waiting room or when attending diabetes education group sessions. Patients will receive a study outline and will be offered participation in the study. At the hospital site’s group diabetes education sessions, the recruiter will discuss the risk of progression to T2DM and outline the study. Eligibility screening will be carried out for all interested women, and consent forms will be provided at the session or mailed after the session. If a woman is not interested in participating at first approach or withdraws at any other stage of the study, the reasons for her decision will be sought.

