## Consent

Eligible women will be given a Participant Information and Consent Form (PI&CF) to review with the recruiter. If there is inadequate time to review the PI&CF, a copy will either be provided directly to the participants or mailed to them along with a prepaid envelope in which to return the completed consent form. If the consent form is not received within four weeks, the recruiter will make contact with the woman. At three months postpartum for all live births, the MAGDA-DPP recruiter will follow up with a phone call to verify if an OGTT at six to eight weeks postpartum has been performed. At three months postpartum and onwards, if the woman does not have diabetes, the study nurse/phlebotomist will make contact to organize for baseline data collection. Once the results of the baseline blood tests are known, women with confirmed diabetes will be informed, referred to their nominated GP and excluded from the study. If they do not have diabetes, they will be randomized into either the control or the intervention group. The recruitment flowchart is shown in Figure 1.

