### Sample size and power calculation

For the estimation of sample size for two groups, using a two-sided 5% significance level and 80% power, the total number required will be 430 (215 in each arm). The sample size calculation was based on the observed mean change in FPG over 12 months in the Greater Green Triangle Diabetes Prevention Program (GGT DPP) study [36] and is powered to detect an effect size of 0.27 (assuming mean difference between intervention and control groups of 0.14 mmol/L and within group standard deviation of 0.5 mmol/L). To allow for an estimated attrition rate of up to 25% (estimate based on the GGT DPP), we will require a total sample of 574 (287 in each arm). This sample size will provide sufficient power to also analyze changes in weight and waist circumference. The intention-to-treat (ITT) principle will be adhered to, and sensitivity analysis will also be carried out.

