### Data analysis

Analyses will be performed using STATA version 12 or later (Stata Corp., College Station, TX, USA) and the ITT principle will be adhered to. Baseline characteristics will be compared between the intervention and control groups using χ^2^ tests, independent t-tests, and/or the Wilcoxon rank-sum test, as appropriate. Primary and secondary outcome (as described above) will be evaluated using mixed models, treating ‘group’ as a between-subject factor, and ‘time’ as a within-subject factor. Two-sided tests will be used, with a level of *P*<0.05 determining statistical significance.

A separate and parallel economic evaluation protocol will be described elsewhere.

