### Trial status

Recruitment in Melbourne (Victoria) commenced at The Royal Women’s Hospital in January 2011, followed by Sunshine Hospital in November 2011 and in Adelaide (South Australia) at Lyell McEwin Hospital in January 2012. By June 4, 2013, 1,517 women diagnosed with GDM have been approached during their clinic appointments at the above three hospitals. Of these, 340 women have given written consent, 219 have not yet returned their consent form, 701 have declined to participate in the study and 257 were ineligible. Recruitment, both retrospectively and prospectively, at Women’s and Children’s Hospital and Flinders Medical Centre in Adelaide is expected to commence in mid-2013.

Baseline testing commenced in July 2012 in Melbourne (Victoria) and March 2013 in Adelaide (South Australia). By June 4, 2013, 134 women had been randomized to either the intervention or the control group. The first MAGDA-DPP intervention group started in November 2012, and there have been six groups, four in Melbourne (Victoria) and two in Adelaide (South Australia), initiated since then.

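### Baseline may fall anywhere from 3 to about 20 or more months after delivery, and the stated outcome model has no term for it: a small, avoidable loss of precision, not a bias.

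*Protocol article*

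**What the plan says.** **Entry.** The Consent section has the study nurse or phlebotomist arrange baseline testing "At three months postpartum and onwards", provided the woman does not have diabetes. No latest date is given. Under Recruitment process, two Adelaide hospitals that joined late (Women's and Children's Hospital and Flinders Medical Centre) may also recruit retrospectively, "allowing women diagnosed with GDM after July 1, 2011 to participate in the study". Trial status expects recruitment there to start in mid-2013. It also shows a lag at the first sites: recruitment began in January 2011 in Melbourne and January 2012 at Lyell McEwin Hospital, but baseline testing began only in July 2012 and March 2013 respectively.

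**Randomization.** Blocked lists are kept per venue or stratum. The article does not define stratum and does not mention time since delivery. Allocation follows receipt of the baseline blood results.

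**Analysis.** "Primary and secondary outcome (as described above) will be evaluated using mixed models", with group as the between-subject and time as the within-subject factor. No covariate is named. The primary outcome rests on change in FPG, weight or waist circumference.

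**Planning.** The sample size, "using a two-sided 5% significance level and 80% power", "is powered to detect an effect size of 0.27" in FPG change. No effect size or SD is given for weight or waist.

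**The concern.** The recruitment rules create an unusually wide spread in one baseline variable. A woman tested three months after birth and a woman tested well over a year after birth may be on different courses of weight and waist over the next 12 months, with or without the programme. If so, part of the within-arm variance in change is predictable from a date the trial already holds. A model with group and time alone leaves that part in the residual.

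Two things are then lost. Confidence intervals for the group difference in change are wider than they need be, and a chance imbalance in time since delivery is not adjusted for. Pre-specifying the term also removes the option of deciding on adjustment after the results are seen. That matters here because a significant result on any one of three endpoints counts as evidence, with no correction for multiple testing.

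**Working it through.** **1. Spread of time since delivery at baseline.** Assumptions: diagnosis at 24 to 28 weeks and delivery at 40 weeks, so delivery comes 12 to 16 weeks after diagnosis.

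- Lower end: 3 months (Consent section).
- Late Adelaide sites, diagnosis on 1 July 2011: delivery falls between 23 September and 21 October 2011. Months since delivery are 19.4 to 20.3 on 1 June 2013, 21.3 to 22.2 on 31 July 2013, and 26.3 to 27.3 on 31 December 2013. If diagnosis was at 20 weeks, the June to July 2013 figures are 18.4 to 20.4 months.
- First Melbourne site, diagnosis in mid-January 2011 at 26 weeks: delivery about 23 April 2011. Testing on 1 July 2012 at the earliest gives 14.3 months.
- Lyell McEwin Hospital, diagnosis in mid-January 2012 at 26 weeks: delivery about 22 April 2012. Testing on 1 March 2013 at the earliest gives 10.3 months.

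The range of 3 to about 20 or more months holds, and late entry is possible at prospective sites too. These are extremes. The documents do not give the distribution.

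**2. The plan's own sample size.** n per arm = 2(1.960 + 0.842)² / d². With d = 0.27 this is 2 × 7.849 / 0.0729 = 215.3, against 215 stated (216 if rounded up). Attrition of 25%: 215 / 0.75 = 286.7, so 287 per arm and 574 in total, as stated. The inputs in brackets, "assuming mean difference between intervention and control groups of 0.14 mmol/L and within group standard deviation of 0.5 mmol/L", give 0.14 / 0.5 = 0.28 and 201 per arm. The stated size therefore follows from 0.27, which is used below.

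**3. What adjustment could gain.** Let R² be the share of within-arm variance in 12-month change explained by time since delivery. The documents give no value, so R² is assumed. The residual SD is multiplied by √(1 − R²), and

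power = Φ( d√(n/2) / √(1 − R²) − 1.960 ), with d√(n/2) = 0.27 × √107.5 = 2.799.

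| R² (assumed) | √(1 − R²) | CI narrower by | Power, 215 per arm | n per arm for 80% |
|---|---|---|---|---|
| 0 | 1.000 | 0% | 79.9% | 216 |
| 1% | 0.995 | 0.5% | 80.3% | 214 |
| 5% | 0.975 | 2.5% | 81.9% | 205 |
| 10% | 0.949 | 5.1% | 83.9% | 194 |

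The interval-width column applies to any of the three endpoints at the given R². The power and sample-size columns use the FPG planning figures and only illustrate what might happen for weight and waist.

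**4. Form of the term.** For woman i with covariate X, let a main effect b·X enter the model at both visits. The change from baseline to 12 months then contains b·X − b·X = 0, so a main effect alone explains none of the variance in change. The covariate must interact with time (adding c·X at 12 months only), or enter a model of the 12-month value that adjusts for baseline.

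**The case against.** The strongest objection is that this is a suggestion for a document we have not seen. A journal article condenses the full protocol, and covariates are commonly left to that document or to the SAP. The Data analysis section names a model family and two factors. It does not say that the analysis is unadjusted, and the sample size section promises sensitivity analysis. This stands: a reader might infer that the trial decided to ignore time since delivery, and the text does not support that. What can be said is that the model as stated does not include it.

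Second, no section says that change in weight, waist or FPG depends on time since birth. This also stands. The link is a plausible premise for weight and waist, not a documented fact, and it is weaker for FPG. The article does not show whether the planning SD of 0.5 mmol/L, taken from another programme, already contains such variation.

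Third, the share of late entrants is unknown. Retrospective recruitment back to July 2011 applies to two hospitals only. On 4 June 2013, 134 of 574 women had been randomized, leaving 440 (77%) to come as those hospitals were due to open. That leaves room for late entrants but does not count them.

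Fourth, if late entrants cluster at particular sites, the venue lists already balance timing in part, and the undefined stratum might do more.

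None of this removes the narrower point. The trial's own recruitment rules create the spread, the stated model has no term for it, and adding one is cheap.

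**Conclusion.** The point holds as a minor improvement in precision. Baseline can fall from 3 to about 20 or more months after delivery, given the assumed gestational ages, and the stated model has no term for this.

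Two stronger readings should be resisted. One is that the comparison is biased: women are randomized after baseline testing, so time since delivery is balanced in expectation, and chance imbalance is already reflected in the confidence interval. The other is that a definite amount of power is being lost. The size depends on an R² that the documents do not give. The illustrative gain is 0.4 percentage points at 1%, 2 points at 5% and 4 points at 10%, and it borrows the FPG effect size although the mechanism mainly concerns weight and waist. The stated sample size is not called into question by this.

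**What to change.** In the Data analysis section, or in the SAP if that is where covariates are fixed, pre-specify months since delivery at baseline for the models of weight, waist circumference and FPG. Enter it as a continuous variable, for example log-transformed. Use either its interaction with time in the mixed model, or a covariate in a model of the 12-month value that adjusts for the baseline value. Include the randomization venue or stratum in the same models.

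The cost is one or two sentences and a few extra parameters, set against 430 evaluable women. The call at three months postpartum already requires the delivery date for women recruited in pregnancy. For women found retrospectively, confirm that the date is recorded. The choice should be fixed before anyone sees outcome data by arm.

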## Consent

Eligible women will be given a Participant Information and Consent Form (PI&CF) to review with the recruiter. If there is inadequate time to review the PI&CF, a copy will either be provided directly to the participants or mailed to them along with a prepaid envelope in which to return the completed consent form. If the consent form is not received within four weeks, the recruiter will make contact with the woman. At three months postpartum for all live births, the MAGDA-DPP recruiter will follow up with a phone call to verify if an OGTT at six to eight weeks postpartum has been performed. At three months postpartum and onwards, if the woman does not have diabetes, the study nurse/phlebotomist will make contact to organize for baseline data collection. Once the results of the baseline blood tests are known, women with confirmed diabetes will be informed, referred to their nominated GP and excluded from the study. If they do not have diabetes, they will be randomized into either the control or the intervention group. The recruitment flowchart is shown in Figure 1.

**Figure 1 F1:**
[figure not shown]
Recruitment flowchart.

### Randomization

Block randomization will be implemented and separate randomization lists for each ‘venue’ or ‘stratum’ will be created. Each list will be supplied as a separate file and will be imported into the current MAGDA management database, which selects the next available sequence number for the venue/stratum. This sequence number will be displayed, along with the assignment code (control or intervention) to the user in the randomization office at Deakin University.

Women will be randomized into either the intervention or control arm after the baseline blood results have been received by the MAGDA-DPP project manager. If the woman does not have diabetes, the project manager or senior program manager will randomize her using the MAGDA-DPP management database. Each woman will receive a letter with the outcome of her randomization along with her baseline test results, and a copy will be sent to her nominated GP.

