### Anthropometric measurements and laboratory testing

To ensure that the clinical measurements meet research standards, measurements will be carried out by specially trained study nurses/phlebotomist. All clinical tests will follow the latest international recommendations from the European Health Risk Monitoring protocol [27]. Blood samples will be collected by the study nurse/phlebotomist, and analyzed by Melbourne Pathology (Victoria) or ClinPath (South Australia). Anthropometric measurements including height, weight, waist and hip circumference, and blood pressure will be taken. Women will be asked to fast from 10 pm the night before their appointment and venous samples will be drawn at the appointment to analyze lipids (triglycerides, total cholesterol, low-density lipoprotein and high-density lipoprotein cholesterol), HbA1c and glucose (fasting and 2 hour OGTT). Additional blood from women who consent to having their blood stored will be bio-banked at −80°C for further additional analyses.

For the intervention group only, at three months after baseline testing or as soon as possible after the final group session, a follow-up assessment will repeat all blood tests (except OGTT), and anthropometric measurements of weight and waist circumference. All women who complete this clinical testing will receive a standardized feedback letter documenting their results and any evidence of high blood pressure or depression. A copy will be sent to their nominated GP.

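### Randomisation is blocked within venue or stratum, but the model as described names only group and time, so a small amount of precision may be forgone

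*Protocol article*

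**What the plan says.** The Randomization section of the protocol article states: "Block randomization will be implemented and separate randomization lists for each" venue or stratum. The lists are loaded into the trial database, "which selects the next available sequence number for the venue/stratum". The number of strata and the block size are not given, and the section does not say what a venue is.

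The Data analysis section says that primary and secondary outcomes "will be evaluated using mixed models, treating ‘group’ as a between-subject factor, and ‘time’ as a within-subject factor". Neither that section nor the sample size section mentions venue, site or stratum. The sample size section refers to a sensitivity analysis but does not describe it.

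Two other passages bear on whether venue could matter:
- Blood samples are "analyzed by Melbourne Pathology (Victoria) or ClinPath (South Australia"), so the laboratory differs by state.
- For two Adelaide hospitals that joined late, the Recruitment process section says that "retrospective as well as prospective recruitment will take place at these hospitals only", reaching back to diagnoses after July 1, 2011. The Trial status section expects recruitment there to begin in mid-2013.

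**The concern.** Blocking within strata keeps the arms balanced in each stratum, so differences between strata drop out of the true sampling variance of the arm comparison. A model without the strata leaves those differences in the residual variance, and hence in the estimated standard error. If strata differ in mean 12-month change, the reported standard error is larger than the true one. The test then rejects less often than its nominal level, and the precision gained by stratifying is not used.

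There is a plausible route to such differences. Time since delivery at baseline may vary by site:
- Two hospitals may enrol women diagnosed up to about two years before recruitment starts there.
- The Royal Women's Hospital recruited from January 2011, but Melbourne baseline testing began in July 2012.
- Lyell McEwin Hospital recruited from January 2012, but Adelaide testing began in March 2013.

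Weight and waist are two of the three co-primary outcomes, and their course over the next 12 months could depend on time since delivery. What is at stake is efficiency, not validity.

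**Working it through.** **Inputs from the protocol article (Sample size and power calculation).** Two-sided 5% level, 80% power, standardised effect 0.27, 215 per arm (430 in total), 25% attrition, 574 recruited.

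**The plan's own figure.** Per arm, n = 2 × ((1.96 + 0.8416)/0.27)² = 215.3. Rounded up this is 216 per arm, or 432, against the stated 430, so the figure reproduces to rounding. With attrition, 430/0.75 = 573.3, which becomes 574 in two arms of 287. (The printed 0.14 and 0.5 mmol/L give 0.28 and 201 per arm. That is a separate matter, and it makes the stated number larger, not smaller.)

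**Assumption.** Let ρ be the share of the variance of 12-month change that lies between strata, with total variance held fixed. The documents give no value, so the table runs from 0 to 0.10.

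**Formulas.** With 215 per arm, z = 0.27 × √(215/2) = 2.80.
- Standard error without stratum, relative to the true one: 1/√(1 − ρ)
- True type I error without stratum: 2 × [1 − Φ(1.96/√(1 − ρ))]
- Power without stratum: Φ((2.80 − 1.96)/√(1 − ρ))
- Power with stratum: Φ(2.80/√(1 − ρ) − 1.96)

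| ρ (assumed) | SE too large by | Type I error, no stratum | Power, no stratum | Power, with stratum |
|---|---|---|---|---|
| 0 | 0% | 0.0500 | 79.9% | 79.9% |
| 0.01 | 0.5% | 0.0489 | 80.1% | 80.3% |
| 0.02 | 1.0% | 0.0477 | 80.2% | 80.7% |
| 0.05 | 2.6% | 0.0443 | 80.6% | 81.9% |
| 0.10 | 5.4% | 0.0388 | 81.2% | 83.9% |

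At ρ = 0.10, for example, √0.90 = 0.949. Power is Φ(0.84/0.949) = 81.2% without the stratum and Φ(2.80/0.949 − 1.96) = 83.9% with it, a difference of 2.7 points.

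**Simulation check.** This used 4,000 runs per setting, five equal venues, blocks of 4, N = 430 and a change-score analysis. The number of venues and the block size are assumptions.
- ρ = 0: power 79.3% with or without venue, so adding the term costs nothing visible.
- ρ = 0.05: type I error 0.042 without venue and 0.047 with it; power 81.0% and 82.1%.
- ρ = 0.10: type I error 0.040 and 0.051; power 81.6% and 84.3%. The mean model standard error without venue was 0.0963, against an empirical standard deviation of 0.0917. The ratio is 1.05, as the formula predicts.

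**Limits.** The change-score form equals the group-by-time contrast with complete data at baseline and 12 months, the two visits that both arms share. The formulas also assume that the arms stay balanced within strata among the women analysed. Drop-out loosens that balance, which moves the type I error back towards 5% and makes the forgone power somewhat larger. With no balance left, the power forgone at ρ = 0.10 could not exceed about 83.9 − 79.9 = 4.0 points.

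**The case against.** The strongest reply is that this is one sentence in a condensed journal article. It assigns roles to two factors. It does not say that they are the only terms, and it does not exclude venue. Covariates are commonly left to an analysis plan, and none is shown here. This stands to the extent that a reader might infer that the model contains nothing but group and time, which the text does not say. It does not remove the point: the article chose to describe its model by naming factors, and the factor that governed randomisation is not among them.

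A reader might also infer that the use of two laboratories is itself enough to distort the glucose comparison. The documents do not support that. Laboratories are split by state, so a woman who stays in her state has the same laboratory at both visits. A constant offset then cancels in her change, and with it in the group-by-time contrast. Only laboratory drift or a difference in scale would remain.

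Nor is a venue shown to be a recruiting hospital. The intervention curriculum (Table 2) uses the word for the community sites of group sessions. Even if strata are hospitals, the two late-joining sites recruit prospectively as well, so a stratum term would capture time since delivery only in part.

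Finally, the size is assumed and small. At shares of 0 to 2% the power forgone is about half a point at most.

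**Conclusion.** The point holds in a limited form. The design stratifies, and the model as described does not use the stratification factor. If strata differ in mean 12-month change, the standard error is modestly too large and the test slightly conservative. For assumed shares of 0 to 10% of the variance of change, the overstatement is 0 to 5.4%, the type I error 5.0% to 3.9%, and the power forgone 0 to 2.7 points. The stated 80% power is met, to rounding, throughout.

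It would be tempting to read this as a standard error that is wrong whatever the data, or as a threat to the validity of the result. Neither follows. The mismatch is zero if venue does not predict change. Where it exists it lies on the conservative side in expectation, with no bias and no excess of false positives. The conclusion rests on the assumed shares, on near-balance within strata, and on the article's description being the model that will be fitted. The point is minor.

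**What to change.** Add the randomisation stratum and its interaction with time as fixed effects in the primary and secondary mixed models. The interaction is needed because the outcome is change: a stratum main effect alone absorbs differences in level, not differences in 12-month change. State what a venue or stratum is. Pool very small strata, for instance within hospital or state, by a rule fixed before outcome data are analysed by arm. Because the trial is open, there is no unblinding date to which such a rule could be tied. If an analysis plan already includes these terms, a sentence confirming it is enough.

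The variable is already in the randomisation database. The cost is a few degrees of freedom: with five strata, as in the simulation, four extra parameters in the change comparison. The sample size of 430 evaluable and 574 recruited need not change.

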## Methods/Design

### Study design

MAGDA-DPP is a prospective, open RCT to assess the effectiveness of a structured diabetes prevention program (DPP) for women who have had GDM. This trial has an intervention group participating in a DPP and a control group receiving usual care from their general practitioners (GPs) during the same time period. Women will be recruited from two Australian State capital cities, Melbourne and Adelaide.

All women recruited into the study will be followed up for 12 months. At baseline, the women will undergo an assessment consisting of blood tests, anthropometric measurements, and self-reported assessment of health status, diet, physical activity, quality of life, depression and risk perception. The intervention group will be assessed at baseline, and at three and 12 months. The control group will be assessed at baseline and 12 months.

The MAGDA-DPP intervention is coordinated by Deakin University (Melbourne Campus) and is supported by a ‘Partnerships for Better Health’ Grant from the National Health and Medical Research Council of Australia (NHMRC). The project includes multiple study partners, consisting of two state governments, three universities and two non-government organizations. Study partners, recruiting hospitals and relevant ethics approvals are listed in Table 1.

**Table 1 T1:** MAGDA project study partners, recruitment sites and relevant ethics approvals

**Study partner/recruitment site (state)**	**Ethics approval authorities (reference number)**
Deakin University (VIC)	Deakin University human research ethics committee (2010–005)^1^
Flinders University (SA)	Southern Adelaide Clinical Network human research ethics committee (330/10)
The University of Melbourne (VIC)	NA
Department of Health (VIC)	NA
South Australia Health (SA)	South Australia Health human research ethics committee (339/02/2013)
Diabetes Australia Victoria branch (VIC)/NDSS	Deakin University human research ethics committee (2010–005)^1^
GP-Victoria	NA
The Royal Women’s Hospital (Vic)	The Royal Women’s Hospital (10/06)
Sunshine Hospital (VIC)	Melbourne Health (2010.008)
Lyell McEwin Hospital (SA)	The Queen Elizabeth Hospital/Lyell McEwin Hospital HREC (2011109)^2^; South Australia Health human research ethics committee (339/02/2013); South Australia Aboriginal Health research ethics committee (04-10-331)

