### Selection of participants

The inclusion criterion for women is diagnosis of GDM in their most recent pregnancy, with GDM defined by the Australasian Diabetes in Pregnancy Society (ADIPS) criteria: fasting plasma glucose (FPG) of 5.5 mmol/L or higher, and/or 2 hour glucose of 8.0 mmol/L or higher on a 75 g oral glucose tolerance test (OGTT) [3], or a glucose challenge test (GCT) result of 12.0 mmol/L or higher.

The exclusion criteria are: (1) pre-existing diabetes (Type 1 or 2 diabetes mellitus); (2) cancer (not in remission); (3) severe mental illness; (4) substance abuse (illicit drugs); (5) myocardial infarction in the preceding three months; (6) difficulty with English; (7) involvement in another post-natal intervention trial; and (8) pregnancy at post-natal baseline testing or at any point during the 12 months of study involvement.

Once women diagnosed with GDM express interest in the study, the recruiter (the MAGDA-DPP project manager or research assistant) will conduct the first eligibility screening, generally prior to the women delivering their babies. A subsequent post-natal screening will be conducted at time of baseline OGTT, to exclude women who have diabetes at that stage.

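### The article allows the project manager both to recruit and screen women and to release the next assignment from venue-specific blocked lists in an open trial

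*Protocol article*

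**What the plan says.** Four statements in the Protocol article bear on this.

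- **Recruiting and screening** (Selection of participants): "the recruiter (the MAGDA-DPP project manager or research assistant) will conduct the first eligibility screening". This usually happens before delivery.
- **Opening the way to randomization** (Randomization): women are allocated "after the baseline blood results have been received by the MAGDA-DPP project manager". The Consent section gives the gate: "Once the results of the baseline blood tests are known, women with confirmed diabetes will be informed, referred to their nominated GP and excluded from" (that is, from further participation); the others go on to be randomized.
- **Releasing the assignment** (Randomization): "the project manager or senior program manager will randomize her using the MAGDA-DPP management database". On the lists: "Block randomization will be implemented and separate randomization lists for each ‘venue’ or ‘stratum’ will be created". They are imported into the database, "which selects the next available sequence number for the venue/stratum", and that number is shown "along with the assignment code (control or intervention) to the user in the randomization office at Deakin University".
- **Blinding** (Study design): "MAGDA-DPP is a prospective, open RCT".

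The article does not give the block size, say whether it varies, or say who can open the imported list files. An article may leave those details to the full protocol, and their absence is not the point here. The point is the assignment of roles, which the article does state.

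**The concern.** Concealment of allocation works best when the person who releases an assignment has no stake in, and little knowledge of, who comes next. Here one role may talk to a woman about the study, screen her, receive the results that make her ready for randomization, and then press the button. With 1:1 blocks kept separately by venue, past assignments partly reveal the next one. If that person can also choose when a woman is entered, or which of two women at a venue is entered first, entry can be steered on a guess, knowingly or not.

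What is at stake is comparability of the arms. Weight and waist circumference are two of the three co-primary endpoints, and a woman's readiness to change, which a recruiter can sense, plausibly affects both.

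**Working it through.** **1. Can one role hold all the steps?** Steering entry needs three things.

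- *Knowledge of the woman.* The recruiter outlines the study, goes through the consent form with her, and telephones her at three months postpartum, about when baseline testing is arranged (Recruitment process; Consent). The project manager may be that recruiter.
- *Knowledge of past assignments.* Whoever randomizes sees each code that he or she releases, and the trial is open. Two roles may randomize, so one person holds the full sequence only by doing all of it or by learning the rest.
- *A lever.* The results go to the project manager, and the article states no order in which eligible women are to be entered. The stated gate after baseline testing is the diabetes result. Pregnancy at baseline testing is also an exclusion, but it too is a matter of fact. The lever is therefore timing and order, not eligibility.

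Nothing in the article prevents one person from holding all three.

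**2. How well can the next assignment be guessed?** The plan gives no figure for this. Its allocation is 1:1 (287 + 287 = 574; Sample size and power calculation), which is the only input the formulas need besides block size. Block size is assumed and varied.

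For blocks of size 2b, with past assignments at the venue and the block size known:

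- share of assignments known with certainty = 1/(b + 1);
- share guessed correctly by always naming the arm that is behind = [b + 0.5 × (4^b / C(2b, b) − 1)] / (2b).

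For block size 4 (b = 2): certain = 1/3 = 33%; correct = [2 + 0.5 × (16/6 − 1)] / 4 = 2.833/4 = 71%.

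| Fixed block size | Certain | Guessed correctly |
|---|---|---|
| 2 | 50% | 75% |
| 4 | 33% | 71% |
| 6 | 25% | 68% |
| 8 | 20% | 67% |
| 10 | 17% | 65% |

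For randomly varying block sizes with boundaries not marked, simulation of about 400,000 assignments each gave:

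| Block sizes mixed | Certain from the running imbalance alone | Guessed correctly |
|---|---|---|
| 4, 6 | 1.0% | 69% |
| 2, 4, 6 | 0.8% | 70% |
| 4, 6, 8 | 0.2% | 68% |

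Varying the blocks removes almost all certainty but hardly lowers the rate of correct guesses. It cannot stand in for separating the roles.

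**3. Can this be turned into a bias?** No. That needs the share of guesses acted on and the difference in prognosis between women moved forward and women held back. The article gives neither.

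**The case against.** The strongest reply is that the safeguards are ordinary and sound. The lists are supplied as files, the database issues the number, and release takes place in a central office after consent and baseline testing. Both duties name an alternative person (a research assistant for screening, the senior program manager for randomizing), so the overlap may never occur. Nothing says that upcoming assignments can be seen. With 134 women randomized between July 2012 and 4 June 2013, about 12 a month over both cities (134/11), several women waiting at one venue is possible but not shown. All of this stands, and it is why the point is minor.

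A reader might go further in three ways that the document does not support.

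- *That the project manager controls final eligibility*, for instance by applying the exclusions for mental illness, substance abuse or English at the last moment. The article describes no such step after baseline. It says that the post-natal screening is there to exclude diabetes.
- *That the database displays past assignments.* It is said to show the number and code being released; a history view is not described. Knowledge of the past comes from having randomized earlier women and from the open design.
- *That the bias is a known fraction of the planned effect of 0.27.* That effect size is for fasting glucose, while the plausible route is motivation and weight. Nor would any imbalance be wholly beyond analysis, since baseline glucose, weight, waist, self-efficacy and social support are all measured.

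What the reply does not remove is that the article expressly permits the combination, and central release protects only so far as past codes do not reveal the next one.

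**Conclusion.** The point holds in a limited form. The article lets one role recruit and screen, receive the results that open the way to randomization, and release assignments from venue-specific blocks in an open trial. The lever is the timing and order of entry within a venue. Guessing beats chance under every block design tried: about 65-75% correct for fixed blocks of 2 to 10 and about 68-70% for varying blocks, against 50%. These figures assume 1:1 blocks, an assumed range of block sizes, and knowledge of all past assignments at the venue. They describe opportunity, not harm; no bias can be calculated from the document. This is a cheap improvement of minor severity.

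**What to change.** In the Randomization section:

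1. Restrict randomization to the senior program manager, who is already named there, or to another existing member of the randomization office, provided that person has no recruiting or screening role.
2. Require eligibility to be recorded as final in the database before the assignment is displayed.
3. State that women are randomized within each venue in the date order in which their baseline results arrive.

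Varying block sizes should not be relied on as the main remedy. The change uses existing staff and adds one database step. Its small downside is a possible short delay when the designated person is away. At the article's status date, 440 of 574 assignments (574 − 134, or 77%) were still to be made and could benefit.
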